## Abstract

**Background:**

The perimenopausal transition is accompanied by psychiatric symptoms in over 10% of women. Symptoms commonly include depressed mood and anhedonia and less commonly include psychosis. Psychiatric symptoms have been linked to the depletion and/or variability of circulating estradiol, and estradiol treatment reduces perimenopausal anhedonia and psychosis in some women. Estrogen fluctuations may disrupt function in the mesolimbic reward system in some women, leading to psychiatric symptoms like anhedonia or psychosis. The Perimenopausal Effects of Estradiol on Anhedonia and Psychosis Study (PEEPs) is a mechanistic clinical trial that aims to (1) identify relationships between perimenopausal-onset anhedonia and psychosis and neuromolecular markers of mesolimbic reward responses and (2) determine the extent to which estradiol treatment-induced changes in mesolimbic reward responses are associated with alleviation of perimenopausal onset anhedonia or psychosis.

**Methods:**

This study will recruit 100 unmedicated women ages 44–55 in the late-stage perimenopausal transition, sampling across the range of mild-to-high anhedonia and absent-to-moderate psychosis symptoms. Patients will be randomized to receive either estradiol or placebo treatment for 3 weeks. Clinical outcome measures will include symptoms of anhedonia (measured with Snaith–Hamilton Pleasure Scale; SHAPS) and psychosis (measured with Brief Psychiatric Rating Scale; BPRS psychosis subscale) as well as neural markers of mesolimbic reward system functioning, including reward-related fMRI activation and PET-derived measure of striatal dopamine binding. Pre-treatment associations between (1) SHAPS/BPRS scores and (2) reward-related striatal dopamine binding/BOLD activation will be examined. Furthermore, longitudinal mixed models will be used to estimate (1) symptom and neuromolecular trajectories as a function of estradiol vs. placebo treatment and (2) how changes in reward-related striatal dopamine binding and BOLD activation predict variability in symptom trajectories in response to estradiol treatment.

**Discussion:**

This clinical trial will be the first to characterize neural and molecular mechanisms by which estradiol treatment ameliorates anhedonia and psychosis symptoms during the perimenopausal transition, thus laying the groundwork for future biomarker research to predict susceptibility and prognosis and develop targeted treatments for perimenopausal psychiatric symptoms. Furthermore, in alignment with the National Institute for Mental Health Research Domain Criteria initiative, this trial will improve our understanding of a range of disorders characterized by anhedonia, psychosis, and reward system dysfunction.

**Trial registration:**

ClinicalTrials.gov NCT05282277

## Introduction

### Background and rationale {6a}

The lifetime prevalence of affective disorders is two times greater in women than men [1], and reproductive transitions and associated neuroendocrine changes open windows of psychiatric vulnerability [2]. During the menopause transition, women show an increased susceptibility to a range of psychiatric symptoms, including depressed mood and anhedonia [3, 4] and, less commonly, psychosis [5]. Estradiol fluctuations are associated with depressive symptoms [6] and predict heightened risk for perimenopausal affective disorders [7]. Furthermore, estradiol treatment has been shown to alleviate perimenopausal-onset depression [8–10] and psychosis [5, 11] symptoms in some but not all women. While estradiol changes during the perimenopause have been linked to affective and psychotic symptoms, not all women show susceptibility to perimenopausal-onset psychiatric symptoms and response to estradiol treatment is mixed. Thus, research is needed to characterize the neurobiological mediators of susceptibility and response to treatment during the perimenopause.

Preclinical models of menopause suggest changes in striatal dopaminergic neurotransmission may, in part, mediate the relationship between ovarian hormone changes and depressive-like behaviors [12]. However, such findings remain to be validated in clinical studies. The NIMH-funded Perimenopausal Effects of Estradiol on Anhedonia and Psychosis Study (PEEPs), submitted in response to RFA-MH-21-105, aims to characterize the neural and molecular mechanisms, specifically focusing on mesolimbic responses to rewards, by which perimenopausal estradiol treatment influences affective and psychotic symptoms. The overarching goals of this study are to characterize potential neurobiological mediators of perimenopausal-onset anhedonia and psychosis to deliver validated molecular imaging targets to use in future mechanistic clinical trials of novel treatments for perimenopausal-onset psychiatric disorders and to inform future research examining the neural and molecular effects of ovarian hormone fluctuations across female reproductive transitions.

Anhedonia is amongst the most common affective symptoms associated with the menopause transition [13] and is broadly associated with ovarian hormone withdrawal in women and preclinical models of menopause [14]. Whereas psychosis is less common during the menopause transition, late-onset psychotic disorders (e.g., age at onset > 40 years) are twice as prevalent in women [15], with peak psychosis risk around the average age of perimenopause [5]. Both preclinical and human studies have shown an association between greater psychosis-spectrum behaviors and lower estrogen levels in females [5].

Dysfunction in reward salience processing is thought to contribute to both anhedonia and psychosis. Anhedonia is characterized by blunted reactivity to rewards and reduced salience attribution to reward cues [16], processes that are mediated by the mesolimbic dopamine system [17]. Preclinical evidence highlights that dopamine blockade produces anhedonic responses to rewarding stimuli [18]. The magnitude of phasic dopamine release to rewards predicts motivation to work for rewards in humans [19], and those with depression show reduced striatal dopaminergic activity during reward processing [20, 21]. However, other PET studies of dopamine activity in depressed samples have shown mixed findings (e.g., reduced, increased, or similar activity compared to healthy controls), which may be due to heterogeneity of symptoms in samples with major depression [22].

In contrast to the reduced salience attribution to rewards seen in anhedonia, salience attribution to irrelevant stimuli may contribute to psychotic symptoms [16], mediated by aberrant striatal dopamine release [23]. PET imaging studies of psychosis have shown higher baseline dopamine synthesis capacity in psychosis [24] as well as higher spontaneous dopamine release [25]. While distinct profiles of reward system dysfunction contribute to anhedonia and psychosis, dysregulation of the mesolimbic dopamine system may be a common etiological pathway.

Given that estradiol modulates striatal reward responses [26], ovarian hormone fluctuations and eventual depletion during the menopause transition may trigger the onset of aberrant dopamine function and thereby produce anhedonia and/or psychosis symptoms. Similarly, estradiol administration may ameliorate perimenopausal anhedonia and/or psychosis symptoms via its effect on the mesolimbic dopamine system. Importantly, both anhedonia and psychosis are associated with significant functional impairment [27, 28]. The identification of neural and molecular biomarkers sensitive to changes in anhedonia and psychosis severity during perimenopause may be used as mechanistic endpoints in perimenopause clinical trials of novel treatments for these symptoms.

### Approach novelty

Consistent with the NIMH Research Domain Criteria (RDoC) framework, this mechanistic trial uses dimensional measures of anhedonia and psychosis severity to stratify participants and as clinical outcome measures. Studies of transdiagnostic and neurobiologically grounded symptom dimensions have the potential to increase the pace of discoveries related to the pathogenesis and treatment of psychiatric disorders relative to categorical and polythetic approaches that treat diverse illness presentations as equivalent [29, 30]. This study focuses on neural responses to rewards as indices of the RDoC Positive Valence System constructs of approach motivation and initial responsiveness to rewards, constructs related to anhedonia in preclinical models [22, 31] and patient samples [32, 33]. Although psychosis is most commonly subsumed within the RDoC domain of Cognitive Systems [34], the present trial focuses on linkages between psychosis severity and response to estradiol treatment and striatal responses to rewards given associations between psychosis, neural response to rewards, and DA release to irrelevant stimuli [24, 25].

A particular novelty of this trial design is its use of DSM-based exclusion criteria in complement with transdiagnostic inclusion criteria. Disorders that are associated with reward system dysfunction unrelated to reproductive transitions are considered exclusionary (e.g., attention deficit hyperactivity disorder; recent moderate-to-severe substance-use disorders; chronic history of depressive episodes). The intent of this approach is to increase sample homogeneity to specifically target anhedonia and psychosis resulting from reproductive transition-related reward system dysfunction.

### Objectives {7}

The primary endpoints of the PEEPs study are mechanistic, measured via neural and molecular reward responses. Using simultaneous PET-MR imaging, this study will examine striatal blood oxygen level-dependent (BOLD) activation to rewards, measured with fMRI, and reward-related striatal dopamine release, measured with [^11^C]raclopride PET. To elicit a reward response, participants will complete a monetary incentive delay (MID) task during imaging. This task has previously shown sensitivity to altered reward-related dopamine release in a transdiagnostic anhedonia sample [35]. The first study objective aims to characterize the relationship between striatal reward responses and perimenopausal-onset anhedonia and psychosis symptoms at baseline. We hypothesize that anhedonia symptoms will be linked to reduced striatal BOLD activation and decreased task-related dopamine release to rewards. In contrast, we expect psychosis symptoms will be linked to increased striatal activation to rewards and higher baseline (tonic) dopamine release. The second objective of this trial will be to determine the effects of estradiol versus a placebo on perimenopausal-onset anhedonia and psychosis symptoms as well as striatal reward responses. We expect the effects of estradiol will be greater than placebo, as indexed by alleviation of anhedonia and psychosis symptoms and normalization of striatal reward response. We further hypothesize that reductions in *anhedonia* symptoms in the estradiol treatment group will be linked to increased striatal activation and increased dopamine release to rewards, whereas reductions in *psychosis* symptoms will be associated with decreased striatal activation to rewards and reduced tonic dopamine release.

### Trial design {8}

A parallel-group, randomized, placebo-controlled, double-blind superiority trial will be used to determine the effects of 3 weeks of estradiol treatment, relative to placebo, on perimenopausal-onset anhedonia and/or psychosis symptoms and neural and molecular reward responses. The study will enroll 100 participants with at least clinically significant anhedonia, including a range of mild-to-moderate anhedonia and absent-to-moderate psychosis symptoms. Based on screen failures and dropout rates in our prior studies involving PET-MR and perimenopausal depression, we expect to obtain analyzable data from at least 85 participants with two PET-MR scans each.

## Methods: participants, interventions, and outcomes

### Study setting {9}

The study setting is the Department of Psychiatry in the UNC-Chapel Hill School of Medicine.

### Eligibility criteria {10}

The study will include unmedicated, perimenopausal outpatient women ages 44–55 who are in late perimenopause and experiencing anhedonia and/or psychosis symptoms with onset coinciding with perimenopausal menstrual irregularity. To determine participant eligibility, women will undergo initial online and phone screening, the structured clinical interview for the DSM-5 (SCID-5), laboratory testing, and a pelvic exam/PAP test (or a medical records review for an exam within 3 years). Participants must meet the following inclusion criteria to be enrolled in the study:44–55 years old, unmedicated, naturally perimenopausal woman in stage −1 of the Stages of Reproductive Aging Workshop (STRAW) criteria [36, 37]At least mild perimenopausal-onset anhedonia (SHAPS≥20) (Snaith et al. [38])Absent-to-moderate perimenopausal-onset psychosis spectrum symptoms as measured by the Brief Psychiatric Rating Scale (BPRS-Positive Symptom Subscale Score between 6 and 17) (Hafkenscheid [39]; Overall & Gorham [40])

Dimensional measures of anhedonia and psychosis severity are used to stratify participants. With respect to stratification, equal numbers of participants will be recruited into each of the following four strata:Mild-to-moderate anhedonia + absent-to-mild psychosisMild-to-moderate anhedonia + moderate psychosisHigh anhedonia + absent-to-mild psychosisHigh anhedonia + moderate psychosis

Mild–moderate anhedonia severity is defined in this trial as Snaith–Hamilton Pleasure Scale (SHAPS [38]) scores between 20 and 36, and high anhedonia severity is defined as SHAPS>36 (using the ordinal scoring of Franken et al. [41]). There is no widely accepted clinical cut-off on the SHAPS, though a meta-analysis by Trøstheim and colleagues (2020) [42] reported that caseness is indicated by scoring more than 1.96 SDs above the general population, which would correspond to a SHAPS score of 25 or greater (see also Alsayednasser and colleagues [43]). However, in this trial, a SHAPS score cutoff of >20 was used to indicate at least mild, clinically impairing anhedonia, consistent with the cutoff used in the NIMH Fast-Fail Trial for Mood and Anxiety Disorders [38, 44]. The SHAPS has shown adequate psychometric properties in clinical and non-clinical samples [45], and ROC analyses suggest that a SHAPS score of ≥ 20 corresponds to clinically significant anhedonia from a general population sample [38].

Absent-to-mild psychosis severity is defined in this trial as <6 on the Brief Psychiatric Rating Scale (BPRS) positive symptom subscale [39, 40], consisting of four items: conceptual disorganization, suspiciousness, hallucinations, and unusual thought content. This total indicates a score of “very mild” on any two symptoms or at least mild on any one symptom (control samples typically score absent or “very mild” on these items [46]). “Moderate” psychosis will correspond to BPRS positive symptom subscale scores between 6 and 16, representing one standard deviation above the mean score for patients with psychotic major depression [47]. Additionally, at least one subscale item score must be > 4 to ensure that the psychosis symptom is associated functional impairment. Individuals with psychotic major depression typically have BPRS positive symptom subscale scores between 7 and 11, and a score of 6 best differentiates psychotic MDD from nonpsychotic MDD [47].

Participants who demonstrate any of the following criteria will be excluded from participation:Pregnancy or sensitivities to ingredients in the Climara® patch or Prometrium®, or their genericsBilateral oophorectomyBody mass index (BMI) extremes (<18 or >45 kg/m^2^) due to its cardiovascular riskPET-MR contraindicationsUse of psychotropic, hormonal preparations, or medication with unknown mood effectsNo axis I disorder history during the 2 years prior to perimenopause onsetHistory of mood episodes requiring hospitalizationCurrent maniaHistory of suicide attempts within the past year or active suicidal ideation with intent or planNeurological conditions (e.g., seizure/traumatic brain injury/stroke) or brain stimulation in past 6 monthsEndometriosis, undiagnosed ovary enlargement or vaginal bleeding, liver disease, breast cancer, cardiovascular disease, history of blood clots in legs or lungs, porphyria, type I or II diabetes mellitus, malignant melanoma, gallbladder or pancreatic or kidney disease, cigarette smoking, recurrent migraines with auraFirst-degree relative with premenopausal breast cancer, breast cancer in both breasts, or multiple relatives (>3) with breast cancerPoor cardiovascular health as determined by review of medical records and symptoms to rule out chronic, uncontrolled hypertension, history/presence of any heart conditions, dyspnea with or without exertion, orthopnea, chest pain/pressure, sense of rapid or irregular heartbeat/palpitations, exercise intolerance (i.e., METS <4), paroxysmal nocturnal dyspnea, unexplained syncope, unexplained lower extremity edemaCurrent substance use disorder or history of moderate-to-severe substance use disorder within the past 2 years

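### The mandatory BPRS range (6 to 17) excludes every woman who could fill the two absent-to-mild psychosis strata, and the moderate stratum leaves other eligible women unassigned

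*Protocol article*

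**What the plan says.** All of the following is in Eligibility criteria {10} of the protocol article unless another section is named.

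- The criteria are binding: "Participants must meet the following inclusion criteria to be enrolled in the study".
- One criterion is headed "Absent-to-moderate perimenopausal-onset psychosis spectrum symptoms as measured by the Brief Psychiatric Rating Scale", and its numerical form is a "BPRS-Positive Symptom Subscale Score between 6 and 17".
- Recruitment is by quota: "equal numbers of participants will be recruited into each of the following four strata". The strata cross two anhedonia levels with two psychosis levels (absent-to-mild, moderate).
- The lower psychosis level: "Absent-to-mild psychosis severity is defined in this trial as <6 on the Brief Psychiatric Rating Scale (BPRS) positive symptom subscale".
- The upper level: moderate "psychosis will correspond to BPRS positive symptom subscale scores between 6 and 16", followed by the further condition that "at least one subscale item score must be > 4".
- The exclusion list counts having no Axis I history in the two years before perimenopause began as a reason to exclude.
- Trial design {8} sets enrolment at 100 and, like the Abstract, describes a sample running from absent to moderate psychosis.

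**The concern.** The enrolment range and the lower psychosis level are defined on the same subscale and do not overlap. A coordinator applying the criterion would turn away every woman meant for two of the four strata. The first objective correlates psychosis scores with striatal BOLD and dopamine measures at baseline, so the bottom of the psychosis range would be cut off and the planned two-by-two sampling could not be filled.

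The moderate definition raises a second problem. Its ceiling differs from the inclusion ceiling, and its item rule removes women whose totals lie inside its own stated range. These women are eligible but no quota takes them.

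The inverted exclusion is a separate fault in the same section. Taken literally, it removes women with a clean recent history and keeps women with a disorder that preceded perimenopause. Approach novelty and the Discussion state the opposite purpose.

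**Working it through.** **Inputs.** Inclusion 6 to 17; absent-to-mild below 6; moderate 6 to 16 with at least one item above 4; four subscale items; 100 women in four equal strata.

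**Assumption: item scoring.** The article does not give the item anchors. It explains the cut-off as very mild on two items or mild on one. With items scored 1 (absent) to 7:

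- two very mild: 2 + 2 + 1 + 1 = 6
- one mild: 3 + 1 + 1 + 1 = 6

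Both give the stated cut-off of 6. With items scored 0 to 6, both give 2, which does not fit. Scoring from 1 is therefore used below, and 0 to 6 is kept as a check.

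**Step 1: eligible and absent-to-mild.** A score must be at least 6 and also below 6. Listing all 7⁴ = 2401 four-item profiles gives 0 that qualify. The count is also 0 with exclusive bounds and with 0 to 6 scoring. Each stratum holds 100 / 4 = 25 women, so 2 × 25 = 50 places cannot be filled. On 1 to 7 scoring the excluded totals are 4 and 5 (5 profiles). A woman with all four symptoms absent totals 4 and is ineligible under a criterion whose own heading admits her.

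**Step 2: eligible but in no stratum (1 to 7, inclusive bounds).**

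- The smallest total with an item above 4 is 5 + 1 + 1 + 1 = 8, so totals 6 and 7 can never be moderate although the stated range starts at 6. A woman with one mild symptom (total 6) is therefore in neither level.
- Profiles with every item at most 4: 4⁴ = 256. Removing the 5 with totals 4 and 5 leaves 251, with totals 6 to 16.
- Profiles totalling 17: 224, all above the moderate ceiling.
- Unassigned: 251 + 224 = 475 of 1535 eligible profiles. The other 1060 are moderate.

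These count possible score patterns, not patients.

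**Step 3: other readings.** Eligible profiles with no stratum, item rule attached to the moderate level:

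| Eligibility | Moderate | Items 1–7 | Items 0–6 | Totals left out if the item rule is ignored |
|---|---|---|---|---|
| 6–17 | 6–16 | 475 | 619 | 17 |
| 6–17 | 7–15 | 705 | 783 | 6, 16, 17 |
| 7–16 | 6–16 | 241 | 435 | none |
| 7–16 | 7–15 | 471 | 583 | 16 |

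With the item rule attached to the moderate level, a gap remains in every row. If the rule is read as a requirement on all participants (inclusive bounds), only a total of 17 is unassigned. Step 1 is unchanged by any of these readings.

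**Step 4: the exclusion list.** Its lead-in excludes anyone who shows any listed feature. One listed feature is the absence of a recent Axis I history. Approach novelty says that disorders unrelated to the reproductive transition are what should exclude. The two cannot both be applied.

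**The case against.** The best reply is that this is a slip in one numeral. The criterion's heading, the list of strata, the Abstract and Trial design {8} all say that absent psychosis is included, and nothing shows that staff have turned away women scoring below 6. That is plausible, and the loss of 50 places is conditional on the text being followed. But these are operative thresholds in a trial that Trial status describes as recruiting until December 31, 2026. Either the criterion misdescribes what is being done, or half the sampling plan is missing.

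The reply also limits the analytical harm, and that part stands. Sequence generation {16a} does not stratify, no subgroup analyses are planned, and the models in Statistical methods {20a} have no term for stratum. A woman without a stratum can still be randomized and analysed, so the second gap is mainly a quota problem. Nor are all low scorers lost: on 1 to 7 scoring only totals 4 and 5 go. The article gives no distribution of BPRS scores, so the effect on the baseline correlations or their power cannot be calculated.

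Two further points are fair. The statement that totals 6 and 7 can never be moderate depends on the inferred scoring; with items from 0, 5 + 1 + 0 + 0 = 6 would qualify. And other exclusions, such as mood episodes that led to hospital admission and recent moderate-to-severe substance use disorder, would still remove some of the women whom the inverted rule lets in.

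**Conclusion.** The eligibility section is wrong as written and needs correcting. The conflict between the inclusion range and the absent-to-mild definition is firm: it holds under either item scoring and either reading of the bounds, and it affects two of four strata, or 50 of 100 planned women, if the text is applied. The gap at the moderate level holds on the natural reading, with inclusive bounds and the item rule belonging to that level. It then covers totals 6 and 7 (on 1 to 7 scoring), totals 8 to 16 with no item above 4, and total 17. Its size depends on the scope of the item rule. The exclusion on Axis I history contradicts the stated purpose of the exclusions. The consequences concern who is enrolled and the spread of psychosis scores in the first objective, not treatment allocation.

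**What to change.** Amend Eligibility criteria {10} as follows.

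1. Start the BPRS inclusion range at the scale minimum, and state the item anchors. The minimum is 4 on the inferred 1 to 7 scoring, which the sponsor should confirm.
2. Use one upper bound for inclusion and for the moderate level. The sponsor must reconcile 16 and 17.
3. Define the two psychosis levels so that every eligible score falls in exactly one. State whether the item rule belongs to the moderate level or to eligibility, and where a total of at least 6 with no item above 4 goes. Lowering the inclusion floor alone does not close this gap.
4. Reword the Axis I entry so that having such a disorder in the two years before perimenopause onset, and not lacking one, is what excludes.

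The cost is a wording amendment and a check of the screening form, of women already screened and of strata already assigned. The target of 100 does not change. If screening has in fact applied 6 to 17, the absent-to-mild places still have to be filled from the recruitment that remains.
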